### EEG recording and microstate analysis

The resting 30-min EEG signal will be recorded at a 1,000 Hz sampling rate by 32 Ag/AgCl electrodes (Nicolet EEG V32, Natus Neurology, United States) according to the international standard 10–20 EEG system (the detailed sites of 32 electrodes can be seen in Figure 1) at each time point. The impedance between the electrode and the patient’s skin will always be kept below 5 kΩ. EEG monitoring will be stopped when the patient is tired or asleep, and then the patient will be kept awake by stimulating the patient’s earlobe.

The EEG raw data will first be preprocessed offline in MATLAB (Version 2020b, MathWorks Inc., Natick, USA). The preprocessing will mainly consist of 2–20 Hz bandpass filters, 50 Hz notch filters, and down-sampling to 250 Hz. EMG and EEG artifacts will be removed by independent component analysis. Finally, all channels will be re-referenced to the average reference.

After the preprocessing, the 10-min noise-free EEG data will be imported into the Cartool toolbox^1^ for microstate analysis. Global Field Power (GFP) was the standard deviation of the amplitude at each point for all channels, which was used to characterize the instantaneous topographic field strength. When GFP was high, the topographic map maintained a relatively steady state and had a high signal-to-noise ratio (29). Therefore, the topographic maps corresponding to the GFP peak will be selected as the original maps for subsequent clustering analysis in this study. The clustering algorithm will be topographic atomize and agglomerative hierarchical clustering (30) with a range of clusters from 1 to 12. The optimal number of clusters will be determined by the meta-criterion (31). Subsequently, the spatial correlation coefficient between each original map and the microstate template maps will be calculated to determine the microstate category to which the original maps will belong. Then, the microstate time series will be smoothed with time frames set to 8 so that segments that are smaller than 30 ms will be rejected. In the end, four parameters of the EEG microstate will be calculated.

Duration: the average duration for which a microstate remains stable.Occurrence: the mean occurrences of a microstate per second.Coverage: the duration of a microstate divided by the total duration of all microstates.Probability: the probability that a microstate transits to another microstate.

### Follow-up period

Each patient will be followed up for 3 months (T4) after the end of treatment to observe residual effects and delayed adverse effects. Follow-up visits will include outpatient visits, video calls, home visits, and surrogate assessments by other healthcare organizations. The follow-up will include an assessment of CRS-R and a recording of adverse effects. The frequency of follow-up will be every 2 weeks for the first month and once a month thereafter.

### Data safety and management

The medical history, demographic data, behavioral data, MRI data, and EEG data of all patients will be stored in the departmental computer database by the study leader. The Ethics Committee of Beijing Tiantan Hospital will regularly check data security.

### Statistical analysis

IBM SPSS Statistics 26 software will be used for statistical analysis. The measurement data will be tested for normal distribution by using Kolmogorov-Smirnov tests. Data conforming to a normal distribution will be analyzed by ANOVA or repeated measures ANOVA for differences in each treatment group. Data not conforming to a normal distribution will be analyzed by the Kruskal-Wallis H test or Friedman test. *Post hoc* tests will be carried out with Bonferroni. Count data will be expressed as cases or percentages, and differences between groups for count data with all theoretical frequencies greater than 5 will be tested by the chi-square test, otherwise, Fisher’s exact test will be used. *p* < 0.05 will be considered to indicate statistically significant differences.

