**Methods/design:**

The study will investigate the effect and safety of simultaneous joint stimulation (SJS) of taVNS and HD-tDCS for the recovery of consciousness. We will enroll 84 MCS patients and randomize them into two groups: a single stimulation group (taVNS and HD-tDCS) and a combined stimulation group (SJS and sham stimulation). All patients will undergo a 4-week treatment. The primary outcome will be assessed using the coma recovery scale-revised (CRS-R) at four time points to quantify the effect of treatment: before treatment (T0), after 1 week of treatment (T1), after 2 weeks of treatment (T2), and after 4 weeks of treatment (T3). At the same time, nociception coma scale-revised (NCS-R) and adverse effects (AEs) will be collected to verify the safety of the treatment. The secondary outcome will involve an analysis of electroencephalogram (EEG) microstates to assess the response mechanisms of dynamic brain networks to SJS. Additionally, CRS-R and AEs will continue to be obtained for a 3-month follow-up (T4) after the end of the treatment.

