**Withdrawal**	
	1. Recurrent seizures during treatment;
	2. Life-threatening diseases such as severe lung infection, intracranial infections, and cerebral hernia;
	3. Death;
	4. Patient is lost to follow-up.

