### Sample size

The sample size was calculated based on the effective rate. An improvement of at least 3 points in the CRS-R was considered an effective treatment. Previous studies found the effective rate of taVNS was 7% (*n* = 14) (7) and of HD-tDCS was 36% (*n* = 11) (21). Assuming the existence of a synergistic effect, the SJS group will have a higher effective rate of 43%, while the sham stimulation group will have no effect. Therefore, the two-sided 2 × 4 chi-square test in PASS (version 15) was used for the sample size calculation of four groups. The test power (1-β) was 80% and the type I error rate (α) was 5%. The calculated effect size W was 0.436, and then a dropout rate of 20% was considered. Finally, a total of 84 patients will eventually be enrolled, and each group will have 21 patients (Figure 2).

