### Behavioral assessments

The CRS-R was first proposed by Giacino et al. (2) to assess the level of consciousness in patients. The scale with a total of 23 points included six subscales of auditory, visual, motor, verbal, communication, and arousal levels (2). In the study, patients will be evaluated independently by two trained clinicians. They will perform five repeated CRS-R assessments at least 2 weeks before enrollment to clarify the patient’s state of consciousness and clinical diagnosis. Finally, the highest CRS-R score will be taken as the pre-treatment (T0) baseline score. Changes in CRS-R will be assessed at three time points during treatment to reflect the effect of treatment: 1 week (T1), 2 weeks (T2), and 4 weeks (T3) (Figure 4).

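### The named CRS-R tests do not use baseline as a covariate, and the repeated-measures ones drop any patient with a missed visit; a baseline-adjusted mixed model would be better

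*Protocol article*

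**What the plan says.** The Statistical analysis section names the software ("IBM SPSS Statistics 26 software will be used for statistical analysis") and then the tests for continuous data: "Data conforming to a normal distribution will be analyzed by ANOVA or repeated measures ANOVA for differences in each treatment group". If normality is rejected, "Data not conforming to a normal distribution will be analyzed by the Kruskal-Wallis H test or Friedman test". No covariate is attached to any of these tests.

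The primary outcome is CRS-R at T0, T1 (1 week), T2 (2 weeks) and T3 (4 weeks), with T4 at the 3-month follow-up (Abstract, Methods/design). Baseline is measured with care. Under Behavioral assessments there are five repeated assessments, and "the highest CRS-R score will be taken as the pre-treatment (T0) baseline score".

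Two other places bear on missing visits. The Sample size section says "The calculated effect size W was 0.436, and then a dropout rate of 20% was considered" and gives no causes for that figure. The Withdrawal part of Table 1 lists four reasons: "Recurrent seizures during treatment", life-threatening disease, death and loss to follow-up.

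**The concern.** Classical repeated-measures ANOVA, as SPSS runs it in the general linear model, needs a value at every visit in the model. The Friedman test likewise needs complete blocks. A patient scored at T0, T1 and T2 but not at T3 therefore contributes nothing to either. Three of the four listed withdrawal reasons are serious clinical events, which are unlikely to be unrelated to CRS-R. Recurrent seizures during treatment might also be related to the allocated stimulation. If one arm lost more patients for such reasons, the remaining patients in that arm could look better than the arm as randomised.

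The second issue is precision. With 21 patients per arm, baseline CRS-R is likely to be among the strongest predictors of later CRS-R, and it is available for everyone. Repeated-measures ANOVA treats it as one more outcome level, and a one-visit ANOVA or Kruskal-Wallis test on raw scores does not use it at all.

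**Working it through.** **1. The plan's own figures.** Inputs from Sample size: W = 0.436, 2 × 4 chi-square (df = 3), power 80%, alpha 5%, dropout 20%, N = 84. The required noncentrality divided by W² gives 57.35, so 58 patients, and 58 / 0.8 = 72.5, so 73. The stated 84 is not reproduced, but it errs on the large side; that is a separate matter. What counts here is the number left after dropout: 84 × 0.8 = 67.2, about 67 (16.8 per arm). At N = 67 and W = 0.436 the chi-square power is 86%, above the 80% target.

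**2. How many patients could be excluded.** If the whole 20% falls before T3, 84 × 0.2 = 16.8, about 17 patients, leave a T0-T3 repeated-measures analysis. This is an upper figure for dropout, since a patient lost between T3 and T4 still has complete T0-T3 data. Separately, if patients who stay also miss each of T1-T3 with probability 2%, 5% or 10% (assumed), the complete cases are 84 × 0.8 × (1 − q)³ = 63, 58 or 49.

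**3. Cost of not using T0 as a covariate.** The documents give no correlation ρ between T0 and T3, so a range is assumed, with equal variance σ² at both visits. Per patient:

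- change from baseline (the T3-minus-T0 part of the group-by-time term): 2σ²(1 − ρ)
- ANCOVA: σ²(1 − ρ²)
- ratio: 2(1 − ρ)/(1 − ρ²) = 2/(1 + ρ)

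| ρ (assumed) | change / ANCOVA variance | 21 per arm act like |
|---|---|---|
| 0.5 | 1.33 | 28 |
| 0.7 | 1.18 | 25 |
| 0.9 | 1.05 | 22 |

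As an illustration in power terms, take a 2-point difference, SD 3 and 17 completers per arm (all assumed). At ρ = 0.7 a two-sample comparison has about 68% power on change and 75% with ANCOVA. At ρ = 0.5 the figures are 47% and 58%.

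**4. Cost of deleting partial data.** Assume compound symmetry and, per arm, 80% complete, 7% last seen at T2, 7% last seen at T1 and 6% with no post-baseline score. The variance of complete-case ANCOVA at T3, relative to a mixed model with T0 as covariate, is 1.02, 1.03, 1.04 and 1.04 at ρ = 0.5, 0.7, 0.8 and 0.9. For complete-case change the same ratio is 1.36, 1.21, 1.15 and 1.10. At the lower correlations nearly all of the loss comes from the missing covariate; at 0.9 the two sources are about equal.

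**5. Possible bias.** Assume no true effect, SD 3, and dropout after T2 driven by poor T0-T2 change, at 30% in one arm and 10% in the other. In simulation, the complete-case contrast then favours the arm with more dropout by about 0.15 to 0.30 points for ρ from 0.8 to 0.5, and by up to about 0.45 if exactly the worst patients leave. An analysis that uses the T0-T2 scores of the same patients gives about zero. With equal dropout in both arms the bias vanishes.

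**The case against.** Several counter-arguments have force.

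- **Baseline is not ignored.** With T0 as a repeated level, the group-by-time term compares change from baseline, and the responder definition (at least 3 points of improvement) is also relative to T0. A reader might infer that ANCOVA would make 21 per arm act like 41 (21 / 0.51 at ρ = 0.7). That holds only against a raw-score ANOVA at one visit. Against the change contrast the figure is 25.
- **The dropout figure has no cause.** A reader might infer that the planned 20% consists of seizures, severe illness and death. Sample size attaches no reason to it, Table 1 also lists loss to follow-up, and some losses may fall after T3. So 17 is a ceiling on what dropout alone removes, and informative exclusion is a possibility rather than a feature of the plan.
- **Not every named test deletes patients for any missed visit.** A one-visit ANOVA at T3, or the chi-square or Fisher test on the responder rate, loses only patients without that visit.
- **The analysis plan is not shown.** Analysis sets and imputation may be specified there. This stands as far as missing-data rules go, so no criticism is made of their absence. The point rests on the tests that are named.
- **A mixed model is not a complete cure.** It removes bias only if data are missing at random, omits patients with no post-baseline score, and does not define CRS-R after death. This also stands, and it is why the responder rate needs its own rule.

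**Conclusion.** The point holds as a matter of method choice. The named tests leave out baseline as a covariate, and the two repeated-measures options discard patients with partial data. The efficiency loss is moderate: about 5% to 33% extra variance against ANCOVA for ρ between 0.9 and 0.5, plus about 2-4% for deleted partial data under the assumed dropout pattern. Up to about 17 of 84 patients could be excluded through dropout. Any resulting bias depends on dropout differing by arm in a way related to outcome; under the assumptions tried it was a few tenths of a CRS-R point.

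A reader might also infer that dropout leaves the trial underpowered. The documents do not support that: the 20% is built into N, and 67 completers keep the sizing test at 86%. The correlations, SD, difference and dropout patterns are assumptions; the test names, visits, 20% and N are the protocol's. The change is worth making because it is cheap and clearly better, not because the planned analysis is invalid.

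**What to change.** Replace ANOVA / repeated-measures ANOVA for CRS-R with a linear mixed model (SPSS MIXED, available in the named software):

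- outcome: CRS-R at T1, T2 and T3, in all randomised patients with any post-baseline score
- terms: arm, visit, arm × visit, and T0 CRS-R as covariate
- a covariance structure specified in advance
- the arm contrast at T3 as the reported estimate
- a statement that the analysis assumes data missing at random

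Aetiology and time since injury may be added as covariates but are optional.

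For the responder rate, analyse patients in the arm to which they were randomised, and count those withdrawn for seizures, life-threatening illness or death as non-responders.

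The cost is a paragraph of analysis wording, slightly more programming and a covariance structure fixed beforehand. T0 is already collected, so no new data are needed.

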The protocol will include only MCS patients because they have better neural plasticity and benefit more from taVNS and HD-tDCS compared to VS/UWS (9, 44). In addition, the duration of treatment is a key factor influencing the outcome. A meta-analysis summarized eight clinical studies of tDCS for DOC and found better outcomes in patients who received more than five repeated tDCS sessions than those who received only a single stimulation session (45). Wang et al. (9) used taVNS in 12 patients with DOC and none of them showed behavioral improvement after 2 weeks of treatment (9). In contrast, another study using a similar stimulation protocol but a longer stimulation time found that five patients regained consciousness, which might be due to the long-term potentiation of taVNS to increase excitatory synaptic connections (8). Therefore, 1 month was set as the treatment cycle in the study. For the primary outcome, we hypothesize that the SJS group will show a significant CRS-R increase after 2 weeks of treatment. This increase will be expected to reach its peak at 4 weeks post-treatment and remain during the 3-month follow-up. In contrast, the single stimulation group will show a significant increase in CRS-R only after 4 weeks of treatment compared to baseline. As for AEs, although tDCS and taVNS caused some mild or transient AEs, neither of them induced serious AEs. A review pointed out that the most common AEs of tDCS in patients with stroke were itching, burning sensation, headache, tingling, sleepiness, difficulty in concentration, mild fatigue, skin redness, and dizziness. Likewise, the most common AEs of taVNS were ear pain, headache, tingling, dizziness, skin redness, fatigue, prickling, pressure, itching, and unpleasant feeling (46–48). In this study, we will judge pain AEs by the NCS-R and observe bedside changes in patients’ ears, scalp, expressions, and levels of arousal and sleep to detect their discomfort and fatigue because patients will be unable to subjectively report their symptoms. In addition, if patients exhibit great residual motor function (motor subscale of CRS-R ≥ 3), we will determine the areas of pain induced by stimulation according to the patient’s performance on localization to noxious stimulation.

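### No between-arm test of CRS-R change is fixed as primary: the non-normal fallback has no arm-by-time test, and the hypothesis is worded as within-group significance

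*Protocol article*

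**What the plan says.** The Abstract (Methods/design) sets the primary outcome: "The primary outcome will be assessed using the coma recovery scale-revised (CRS-R) at four time points to quantify the effect of treatment". The time points are T0 to T3, and no visit or contrast is singled out.

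The Statistical analysis section then sets a gate: "The measurement data will be tested for normal distribution by using Kolmogorov-Smirnov tests". If the data pass, "Data conforming to a normal distribution will be analyzed by ANOVA or repeated measures ANOVA for differences in each treatment group". If they fail, "Data not conforming to a normal distribution will be analyzed by the Kruskal-Wallis H test or Friedman test". For post hoc comparisons it says only that "tests will be carried out with Bonferroni", without defining the family. For counts, "differences between groups for count data with all theoretical frequencies greater than 5 will be tested by the chi-square test", with Fisher's exact test otherwise.

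The Discussion gives the hypothesis: "For the primary outcome, we hypothesize that the SJS group will show a significant CRS-R increase after 2 weeks of treatment". By contrast, "the single stimulation group will show a significant increase in CRS-R only after 4 weeks of treatment compared to baseline". The sham arm does not appear in these sentences.

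The Sample size section defines an effective treatment as a CRS-R gain of at least 3 points and sizes the trial with a 2 × 4 chi-square test on that rate.

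**The concern.** The trial randomises patients to four arms, one of them sham, so that recovery common to all arms cancels out. The continuous CRS-R analysis is not written to use this. If each arm is tested against its own baseline and the verdicts are compared, an arm can reach significance through spontaneous recovery alone, and two arms with the same true gain can fall on opposite sides of 0.05 by chance. Patients may enter soon after the first month from injury. The two-week stability criterion limits spontaneous gain but does not exclude it.

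The choice of method is also left to the data. CRS-R is an integer scale with a 23-point maximum, so a normality pre-test is a poor way to decide which question the primary analysis answers. At stake is whether a claim that SJS is superior would rest on the randomised comparison.

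**Working it through.** The plan gives no standard deviation for CRS-R and no figure for this point, so there is nothing of its own to reproduce. The 84 patients were derived for the response rate, not for a continuous contrast. All standard deviations and effects below are assumptions.

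**1. What each named test can answer**

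| Method | Arm factor | Time factor | Arm × time | T0 adjustment |
|---|---|---|---|---|
| Repeated measures ANOVA | possible | yes | possible, not named | not named |
| Kruskal-Wallis | yes | no, one score at a time | no | only if applied to change, not named |
| Friedman | no | yes | no | no |
| Chi-square or Fisher on gain ≥ 3 | yes | no | no | through the change score; not linked to the hypothesis |

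**2. Contrasting two within-arm verdicts**

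Inputs: 21 patients per arm and 20% dropout (Sample size section), so 21 × 0.8 = 16.8, about 17 completers. Two arms have the same true change, expressed as mean change divided by SD of change, and each is tested by a paired t-test at two-sided 0.05.

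If each arm is significant with probability p, independently, then P(discordant) = 2p(1 − p).

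| Standardised change | p, n = 17 (simulated) | 2p(1 − p) | Discordant, n = 17 (simulated) | Discordant, n = 21 (simulated) |
|---|---|---|---|---|
| 0.3 | 0.215 | 0.338 | 0.342 | 0.385 |
| 0.4 | 0.346 | 0.453 | 0.457 | 0.490 |
| 0.5 | 0.497 | 0.500 | 0.500 | 0.486 |
| 0.6 | 0.643 | 0.459 | 0.460 | 0.386 |
| 0.8 | 0.871 | 0.225 | 0.220 | 0.120 |

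By symmetry, about half of the discordant trials favour SJS: 17% to 25% at n = 17 for changes of 0.3 to 0.6. With no true change, discordance is about 10%.

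**3. The same with Friedman in each arm**

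Assumptions: integer scores, 17 per arm, between-patient SD 3, within-visit SD 1.2, and an identical rise of 0.8 to 1.2 points by T3 in every arm. The pattern of SJS significant with at least one single-stimulation arm not significant occurs in 25% to 39% of trials. In the same data, Kruskal-Wallis on the T3 − T0 change across the four arms rejects in 4.2% to 5.2%, close to the nominal 5%.

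**4. What ignoring T0 costs**

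Assumptions: true gains of 3, 1.5, 1 and 0 points in the four arms, with the SDs of step 3. The implied visit correlation is 9 / (9 + 1.44) = 0.86. With 17 per arm, Kruskal-Wallis has 56% power on raw T3 scores and 99% on change. With 21 per arm the figures are 67% and 99.7%. The gap depends on that high correlation and would be smaller with a lower one.

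**The case against.** A reader might infer that the difference in change between arms is never tested, or that the trial will be judged on within-group significance. The documents support neither reading.

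- Kruskal-Wallis is a between-arm test, and the plan does not exclude applying it to change scores. It is valid either way: with an identical 1-point gain in four arms of 21 (assumed SD 3, correlation 0.7), it rejects in 4.5% of trials on raw T3 scores and 5.0% on change. Leaving out baseline costs precision, not validity.
- Repeated measures ANOVA with four arms can give an arm-by-visit term. A condensed article may leave the naming of that term to a fuller document.
- A gain of at least 3 points is a dichotomised change score. The trial is sized on comparing it across arms, and the plan has a between-group test for counts that does not pass through the normality gate.
- The hypothesis stands in the Discussion and describes an expected time course. Only the single-stimulation sentence mentions baseline. It is not a decision rule, so the discordance figures measure what the wording invites, not a procedure that the protocol adopts.

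A reader might also infer that CRS-R will almost always fail the normality test. That depends on choices the plan does not state. With 16 arm-by-visit tests at n = 21 on rounded normal scores, at least one Lilliefors-corrected test rejects in 85% (SD 4) to 98% (SD 2.5) of trials. With uncorrected Kolmogorov-Smirnov critical values the figure is 1% to 3%.

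These objections all stand, and they narrow the point without removing it. None of the available between-arm tests is tied to the primary hypothesis, the fallback has no arm-by-time test, and the one place that spells out the primary hypothesis words it within group. An analysis plan consistent with that wording would carry the weakness forward.

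**Conclusion.** The concern holds in limited form. For continuous CRS-R, no between-arm test of change is fixed as primary. The non-normal branch offers no arm-by-time test and no stated baseline adjustment, and a pre-test on an integer scale selects the branch. Following the hypothesis as worded could rest a superiority claim on two within-arm verdicts. For two arms with equal true gains, these disagree in roughly 34% to 50% of trials with 17 completers per arm and standardised changes of 0.3 to 0.6. The rate is lower outside that range: 22% at 0.8 and about 10% with no change. These sizes rest on assumed SDs and effects. The logical point that a difference in significance does not test a difference needs no such assumption.

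**What to change.** - Remove the normality gate for CRS-R.
- Pre-specify one between-arm analysis adjusted for T0, for example a mixed model of T1 to T3 with arm, visit and arm × visit, and T0 as covariate. Add a rank-based ANCOVA or a proportional-odds model as sensitivity analysis.
- Reword the primary hypothesis as the baseline-adjusted CRS-R difference, SJS minus a named comparator, at a named visit. State whether the two single-stimulation arms are compared separately or together, and where sham enters.
- State how the 3-point response analysis relates to this contrast.
- Keep within-arm tests against baseline as descriptive.

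The cost is analysis wording only. T0 is already collected, and no patients, visits or assessments are added.

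### Post hoc tests use plain Bonferroni; Holm's step-down on the same comparisons keeps the same 5% family-wise error and never rejects fewer hypotheses

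*Protocol article*

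**What the plan says.** In the protocol article, the Statistical analysis section assigns measurement data to ANOVA or repeated measures ANOVA, or to Kruskal-Wallis or Friedman tests when normality fails. It then states that post hoc "tests will be carried out with Bonferroni". It does not say whether a family is all six pairs of the four arms, a subset of them, or the time points within an arm. Count data come after that sentence: chi-square when all expected counts exceed 5, otherwise Fisher's exact test, with no adjustment named. The threshold is p "< 0.05 will be considered to indicate statistically significant differences".

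The Sample size section plans on responders, defined by a CRS-R gain of at least 3 points. It says "Previous studies found the effective rate of taVNS was 7"% "and of HD-tDCS was 36"%, that "the SJS group will have a higher effective rate of 43"%, and that sham has no effect. On the test, "the two-sided 2 × 4 chi-square test in PASS (version 15) was used for the sample size calculation of four groups". The 80% power therefore belongs to the four-group test and not to any pair of arms.

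**The concern.** The Abstract gives the aim as the effect and safety of SJS, and the Introduction argues that one technique alone is not enough. A significant four-group test does not show that SJS beats any particular arm; the post hoc comparisons have to do that. None of them was sized, so their power depends on the arm size and on the adjustment. Plain Bonferroni holds every comparison to the strictest threshold even after others have been rejected. Holm relaxes the threshold after each rejection and gives up no family-wise error control. Any power lost this way is avoidable.

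**Working it through.** **The plan's own figure.** For a 3-df chi-square test at 5% and 80% power the noncentrality is 10.903. N = 10.903 / 0.436² = 57.4, so 58. With 20% dropout, 58 / 0.8 = 72.5, so 73. With equal arms, 15 / 0.8 = 18.75, so 19 per arm and 76 in total. The stated 84 is not reached from the stated inputs. That is a separate matter; 21 per arm is taken as given here, and 21 × 0.8 = 16.8, about 17, as the number left after dropout.

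**The two rules.** With m comparisons, Bonferroni rejects when p ≤ 0.05/m. Holm orders the p-values and compares the i-th smallest with 0.05/(m − i + 1), stopping at the first failure. For m = 6 the thresholds are 0.0083, 0.0100, 0.0125, 0.0167, 0.025 and 0.05. The first equals Bonferroni's and the rest are looser, so Holm cannot reject less.

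**Inputs.** Response rates 43%, 7%, 36% and 0% (Sample size section); 21 or 17 per arm; two-sided tests; family-wise 5%. Power is the share of simulated trials (400,000 per setting) in which the comparison is rejected.

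| Family, test, n per arm | SJS v taVNS, Bonferroni → Holm | SJS v sham, Bonferroni → Holm |
|---|---|---|
| Six pairs, Fisher, 21 | 38.2% → 46.9% | 74.7% → 80.7% |
| Six pairs, Fisher, 17 | 30.7% → 31.4% | 65.0% → 65.0% |
| Six pairs, chi-square, 21 | 53.7% → 61.7% | 94.3% → 94.3% |
| Six pairs, chi-square, 17 | 44.4% → 48.0% | 81.1% → 81.1% |
| Three SJS contrasts, Fisher, 21 | 52.0% → 59.3% | 86.8% → 86.8% |
| Three SJS contrasts, Fisher, 17 | 32.9% → 39.6% | 65.0% → 65.0% |
| Three SJS contrasts, chi-square, 21 | 65.5% → 72.1% | 94.3% → 94.4% |
| Three SJS contrasts, chi-square, 17 | 58.5% → 62.6% | 91.8% → 91.8% |

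SJS v HD-tDCS (43% v 36%) is between 0.6% and 6.8% in every row. Under the plan's own rule for choosing chi-square or Fisher, Holm over six pairs with 21 per arm takes SJS v taVNS from 43% to 53%.

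**Why the SJS v sham gain appears only in one row.** It comes from the discreteness of Fisher's test. With 21 per arm, 7 responders against 0 gives p = 2 × C(21,7)/C(42,7) = 2 × 116,280 / 26,978,328 = 0.0086. That just misses 0.0083 but meets Holm's second threshold of 0.0100. With 17 per arm, 7 against 0 gives 2 × 19,448 / 5,379,616 = 0.0072, which passes already. Six against 0 gives 2 × 12,376 / 1,344,904 = 0.0184, which misses 0.0167 as well.

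**Error rate.** With all four arms at the mean rate, (43 + 7 + 36 + 0)/4 = 21.5%, the chance of any false rejection among the three SJS contrasts is the same under both rules applied to that family: 5.17% each (chi-square, 17 per arm) and 1.39% each (Fisher, 21 per arm).

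**Continuous outcome.** The article gives no SD for the CRS-R, so standardized effects were assumed. With 1.0, 0.8 and 0.3 against the three comparators, 17 per arm and a family of three, power goes from 70.0% to 71.9%, 47.6% to 52.4% and 6.5% to 12.5%. With 0.8 against each, it goes from about 47.5% to 54.7%. Over both families and both arm sizes the gain is roughly 1 to 8 points per SJS contrast.

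**The case against.** Bonferroni controls the family-wise error, so nothing in the section is wrong, and a condensed article may leave the list of comparisons to the full protocol. Both points stand; this is an efficiency gain only.

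The Bonferroni sentence also follows the measurement-data tests, whereas most of the figures above are for responder counts. That stands too. Responder rates are used because they are the only effect sizes the article gives, and the continuous check rests on assumed effects. The property that Holm never rejects less does not depend on the outcome type.

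A reader might infer more: that the plan tests each comparison at 0.0083, and that Holm would lift SJS v taVNS from 38% to 59% (21 per arm, Fisher) at the same error rate. The documents do not support this. No six-pair family is stated. Of that 21-point rise, 14 points (38% to 52%) come from cutting six pairs to three before any step-down is applied. That cut is not neutral: with chi-square at 17 per arm, the error over the three SJS contrasts rises from 2.1% to 5.2%, still nominally 5%, and the other three pairs lose their protection. The Discussion also frames the primary hypothesis as changes from baseline at 2 and 4 weeks, so a rule covering only the three SJS contrasts would leave the time-point comparisons without an adjustment.

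**Conclusion.** The point holds as a free improvement. On any one family, Holm keeps the 5% family-wise error and never rejects less than Bonferroni.

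The size depends on the family and the arm size. With Fisher's test over six pairs it is about 9 points for SJS v taVNS and 6 for SJS v sham at 21 per arm, but about 1 and 0 at 17 per arm. Over three SJS contrasts it is about 7 points for SJS v taVNS at either arm size and none for SJS v sham. These figures rest on the planning rates being true and on responder counts standing in for the CRS-R score.

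It would be wrong to conclude that Holm rescues the comparison with HD-tDCS. At 43% v 36% its power stays at about 7% or less under every adjustment tried; that is a matter of sample size.

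**What to change.** In the Statistical analysis section, replace Bonferroni with Holm-adjusted Bonferroni for every post hoc family, between arms and between time points, and keep each family as planned. State which comparisons each family contains, since the adjustment is undefined without that. The change should be made before unblinding. It needs no extra patients, visits or data, and the adjusted values come from the same unadjusted p-values.

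Restricting the confirmatory between-arm family to SJS v taVNS, SJS v HD-tDCS and SJS v sham is an optional further choice. It raises power on those contrasts in most settings but gives up formal tests of the other three pairs, including each single technique against sham. The sponsor should decide it on its own merits; it is not part of the free change.
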